**Discussion::**

There is no consistent conclusion about the pathogenesis of wake up stroke. Wake up stroke is more likely to manifest as small vessel disease. The incidence of wake up stroke patients is relatively high, and the effectiveness and safety of intravenous thrombolysis under the guidance of multimode imaging therapy in wake up stroke need to be further explored by prospective, large-scale studies.

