## Introduction

1

The patient was normal when he fell asleep at night, but after waking up, he developed stroke symptoms.^[1]^ This phenomenon was defined as wake up stroke (WUS). Due to the inability to accurately determine the actual time of onset of this part of patients, according to the criteria of stroke diagnosis and treatment guidelines, this part of patients are often excluded from recombinant tissue plasminogen activator (rt-PA) treatment. WUS is relatively common clinically, accounting for about one-quarter of patients with new-onset ischemic stroke,^[2]^ but the statistical data obtained by different studies are quite different. A population-based study in the United States in 2005 found that^[3]^ nearly 58,000 WUS patients in the United States were seen in the emergency department in 2005. The CASPR report^[4]^ the data of 11 hospitals in 5 different areas of California surveyed by it showed that the proportion of WUS accounted for about 8% of ischemic stroke, other states such as Houston is about 6.4%, Boston is about 27%.^[5,6]^ A 4-year study in the UK found that the incidence of WUS is about 25% (135/545).^[7]^ The stroke registration from Canada found that WUS accounted for 13.5%.^[8]^ Lausanne, Switzerland, reported that the incidence of WUS was as high as 33.1%.^[9]^ In the Asian region, Japan and South Korea accounted for 9.7% and 27.8% of WUS occurrences.^[10,11]^ China currently lacks epidemiological surveys on WUS. Although it is currently difficult to draw a uniform ratio from the existing statistical data, we can find that WUS is more common clinically. Data from clinical and imaging studies indicate that the onset time of most patients with ischemic stroke is between 6:00 and 12:00 in the morning,^[12]^ showing a peak in the morning. Therefore, scholars speculate that there may be a considerable proportion of WUS patients whose onset time is close to awakening, and there is still the possibility of thrombolytic therapy. In recent years, multimodal imaging techniques have been used to evaluate the ischemic penumbra after cerebral ischemia in WUS patients, thereby guiding thrombolytic therapy.^[13]^ There have been some clinical studies based on multimodal imaging techniques to guide WUS thrombolytic therapy and found that a considerable portion of WUS patients can benefit from thrombolysis,^[14]^ but most of these studies are relatively small samples and are observational studies. The use of rt-PA thrombolytic therapy in the early stage is one of the most effective treatment methods for acute cerebral infarction, but due to the limitation of time window, the proportion of patients benefiting is not high. Although the European Acute Stroke Collaboration Study extended the time window for intravenous thrombolysis, the proportion of thrombolysis in China is still <2%.^[15]^ Whether WUS can be used for thrombolytic therapy is still controversial. Therefore, this study will combine the imaging technology to assess the onset time of WUS patients, and analyze the imaging characteristics of WUS patients and patients within the time window suitable for thrombolytic therapy.^[16]^ This study aimed to observe the efficacy of intravenous thrombolysis in WUS patients.

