#### Inclusion criteria

2.3.2

Time of onset: last appeared to be normal until symptoms will be found <12 hours and >4.5 hours;The patient was found to be awake or witnesses found neurological deficits;NIHSS score ≥4 points;No changes or early changes are insufficient to the one-third distribution area of the middle cerebral artery;DWI/FLAIR imaging performance mismatch (DWI imaging and FLAIR imaging);All other indications for intravenous thrombolysis;Patients with large vessel occlusion are treated with endovascular treatment. The treatment principles refer to “Chinese Expert Consensus on Intravascular Treatment of Acute Ischemic Stroke.”

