#### Exclusion criteria

2.3.3

Patients will be excluded if they meet the following criteria:

Severe patients with malignant hypertension, severe arrhythmia, and acute myocardial infarction;Patients with recent acute infection, trauma, surgery, diabetic ketoacidosis, and hyperosmolar coma;Liver patients with severe primary diseases such as kidney, hematopoietic system, and so on;Patients with tumor and other organ failures.

One of the above is excluded.

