#### Grouping method

2.4.2

We will be divided into awakening stroke group (wake group whose morbidity is not exact) and ischemic stroke group (the group clarifying the time of onset) according to whether the onset time of the patient is clear. The awakening group is divided into the awakening group with thrombolytic therapy and the awakening group without thrombolysis according to whether they receive thrombolytic therapy.

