#### Treatment solutions

2.5.2

Patients in the defined time-onset group will be given intravenous thrombolysis. The awakening group performs multimodal magnetic resonance imaging (MRI) screening (DWI and FLAIR) on the basis of meeting the pre-set conditions. If the MRI indicates that the DWI-FLAIR does not match, intravenous thrombolytic therapy will be given; if the MRI shows DWI-FLAIR matching, it will be given general treatment. Intravenous thrombolysis uses rt-PA. One-time dosage is 0.9 mg/kg, and the maximum dose does not exceed 90 mg. First, a 10% dose of intravenous bolus was given, and the rest of the dose continued to be infused intravenously for a total of 60 minutes. Thrombolysis is completed in the intensive care unit of the neurology department. During the thrombolysis process, the patient's consciousness and changes in limb muscle strength are closely observed. During this period, we will monitor patients’ vital signs, blood oxygen saturation, and give them treatments such as free radical scavenging and stable plaque. Recheck the computed tomography (CT) of the brain after 24 hours. If no intracranial hemorrhage is found, antiplatelet aggregation treatment (0.1 g oral aspirin tablets) should be given, and acupuncture and rehabilitation should be given after the condition is stable. Patients in the WUS group without thrombolysis received aspirin 300 mg orally as soon as possible after admission, and then changed to 100 mg/day. Other treatment methods will be the same as those of thrombolytic therapy.

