#### Safety evaluation after thrombolysis

2.6.1

The occurrence time, treatment measures, and results of various adverse events such as intracranial hemorrhage, skin, gums, and digestive tract in patients undergoing thrombolytic therapy are recorded by specialized personnel. The safety of thrombolytic therapy is mainly evaluated by the incidence of intracranial hemorrhage. During thrombolysis, if there is headache, vomiting, and other suspected intracranial hemorrhage or other parts of the bleeding, stop thrombolysis immediately. At the same time, review the head CT. If there is no symptom of appeal, the head CT is reviewed 24 hours after thrombolysis. The significant deterioration of nerve function caused by intracranial hemorrhage (increased NIHSS score ≥4 points) will be considered as symptomatic intracranial hemorrhage.

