#### Evaluation of efficacy and prognosis

2.6.2

A trained neurologist who will be unaware of the patient's morbidity was evaluated by the National Institutes of Health Stroke Scale (NIHSS score) at the time of patient admission, 24 hours after treatment, and 7 days after treatment. After discharge, the patient's prognosis was evaluated by the modified RanKin scale (mRS). We defined mRS score 0 to 1 points as cured and 0 to 2 points as good prognosis. After 7 days of treatment, the NIHSS score is reduced by 4 points and it is considered that it will be judged as effective in the early stage, and the NIHSS score is increased by 4 points or death will be judged as invalid or worse (Table 1).

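### Patients given endovascular treatment appear to be in the analysis, with their efficacy and bleeding results credited to rt-PA; the size and direction of the distortion cannot be determined from the article

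*Protocol article*

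**What the plan says.** All references are to the protocol article.

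- **Aim (section 1).** "This study aimed to observe the efficacy of intravenous thrombolysis in WUS patients".
- **Eligibility (2.3.2 and 2.3.3).** The inclusion list contains "Patients with large vessel occlusion are treated with endovascular treatment", with an expert consensus cited for the treatment principles. The exclusion list, which ends with "Patients with tumor and other organ failures", names neither large vessel occlusion nor endovascular treatment.
- **Treatment (2.5.1 and 2.5.2).** Known-onset patients get rt-PA. Wake-up patients get rt-PA if DWI and FLAIR are mismatched and general treatment if they match. Endovascular treatment appears in neither section. Of the wake-up group without thrombolysis, 2.5.2 says "Other treatment methods will be the same as those of thrombolytic therapy".
- **Groups (2.4.2).** Patients are first split by whether onset time is known. Then "The awakening group is divided into the awakening group with thrombolytic therapy and the awakening group without thrombolysis according to whether they receive thrombolytic therapy".
- **Safety (2.6.1).** "The safety of thrombolytic therapy is mainly evaluated by the incidence of intracranial hemorrhage". Adverse events are described as recorded in patients who undergo thrombolysis.
- **Efficacy (2.6.2).** NIHSS at 24 hours and 7 days, and mRS: "We defined mRS score 0 to 1 points as cured and 0 to 2 points as good prognosis". Nothing distinguishes patients who had an endovascular procedure.
- **Analysis (2.8).** Between-group tests are unadjusted. The treatment effect itself is to be evaluated by the Wilcoxon signed rank test, which is a paired, within-group test.

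**The concern.** The question is what rt-PA does in wake-up stroke. Endovascular treatment is a second reperfusion treatment that can change NIHSS and mRS and can itself be followed by intracranial haemorrhage. If patients who receive it are analysed together with the rest, an improvement or a bleed after the procedure is counted as a result of thrombolysis.

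Two things are at stake. The first is the between-group contrast, if the share of patients given endovascular treatment differs between groups. The second is everything read from the thrombolysed patients alone: the before-after efficacy test and the absolute haemorrhage rate. No comparison group offsets the endovascular contribution there.

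**Working it through.** The article states no sample size, event rate, occlusion share or endovascular rate, so there is no figure to reproduce. The check has two parts: the sections set side by side, then an illustration in which every number is assumed.

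**1. Are these patients in the analysis?**

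The endovascular sentence stands under the inclusion criteria, the exclusion criteria do not remove occlusion, and no visible text sends such patients out of the comparison. On the plain reading they are in. Section 2.5.2 leaves them unaccounted for: it offers only rt-PA or general treatment, and the general treatment in 2.5.1 covers oxygen, cardiac monitoring, temperature, blood pressure, glucose and nutrition. The endovascular sentence also shares a list with DWI/FLAIR mismatch and the other indications for thrombolysis. Taken literally, it therefore applies to thrombolysis candidates, while 2.5.2 says the remaining treatment is the same in the group without thrombolysis. These statements need reconciling.

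**2. Does anything balance endovascular use?**

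Sections 2.1 and 2.7 speak of randomization and sealed envelopes. Sections 2.4.2 and 2.5.2 give rt-PA by onset type and DWI-FLAIR status. As the treatment is described, chance does not decide who gets rt-PA, so endovascular shares can differ between groups.

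**3. Illustration: between-group difference**

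Suppose rt-PA has no effect. Let qT and qC be the endovascular shares in the thrombolysed and comparison groups, and g the gain in mRS 0 to 2 among those who have the procedure.

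False difference = (qT − qC) × g, with g assumed to be 10 to 30 points.

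| qT | qC | Calculation | False difference |
|---|---|---|---|
| 20% | 20% | 0 × g | 0 |
| 30% | 20% | 0.10 × 0.10 to 0.10 × 0.30 | 1 to 3 points |
| 40% | 10% | 0.30 × 0.10 to 0.30 × 0.30 | 3 to 9 points |
| 10% | 30% | −0.20 × 0.10 to −0.20 × 0.30 | −2 to −6 points |
| 10% | 40% | −0.30 × 0.10 to −0.30 × 0.30 | −3 to −9 points |

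The sign depends wholly on which group has more endovascular treatment.

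**4. Illustration: absolute haemorrhage rate**

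Let e be the excess haemorrhage risk due to the procedure, assumed to be 1 to 5 points.

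Excess credited to rt-PA = qT × e.

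- Low: 0.10 × 0.01 = 0.001, or 0.1 points.
- High: 0.40 × 0.05 = 0.020, or 2.0 points.

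The comparison group's share is not in this formula, so equal shares do not remove the excess.

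**5. Within-group efficacy test**

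The same logic applies. In terms of mean NIHSS change, the endovascular contribution is qT times the extra change due to the procedure, and nothing is subtracted from it. The article gives no figure for that change, so none is put in here.

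**The case against.** **The sentence may mean diversion.** It is worded as a management statement and could mean that patients with occlusion leave for endovascular treatment and are not compared. That would fit the silence of 2.5.2, and the flow chart that might settle it (Figure 2) is not shown. This stands as a real alternative. On that reading the fault is a misplaced and unclear eligibility rule rather than a mixed effect, and 2.3.2 still needs correcting.

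**Equal background care does not bias a contrast.** This is correct. If wake-up patients were truly randomized to rt-PA or not, with equal access to endovascular treatment, the between-group bias would vanish, as the first row of the table shows. A reader might infer that the problem would survive any repair of allocation. For the between-group wake-up comparison the document does not support that. What would survive is the effect on the within-group test and on the absolute haemorrhage rate.

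**The direction is not known.** The abstract's remark that "Wake up stroke is more likely to manifest as small vessel disease" might lead a reader to infer systematically fewer endovascular procedures in the wake-up groups than in the known-onset group. The document does not carry that far. The remark is general, and enrolled patients are selected on NIHSS and imaging. The two-centre study summarised in section 3 found higher admission NIHSS in wake-up patients, which does not suggest fewer severe occlusions. Known-onset and mismatched wake-up patients also both receive rt-PA, so the contrast between them does not estimate an rt-PA effect anyway.

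**Adjustment belongs in the analysis plan.** In part, yes. A condensed article may leave stratification and case report form fields to a fuller document, and their absence here is not the point. Eligibility and the reading of haemorrhage as the safety of thrombolysis are fixed in this text.

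**Conclusion.** The point holds in a limited form. As written, the article places patients who receive endovascular treatment in the trial, does not account for them in the treatment section, and reads their outcomes as results of rt-PA. Since rt-PA is given by onset type and DWI-FLAIR status, endovascular use may differ between groups. The before-after test and the absolute haemorrhage rate are affected even if it does not.

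The size and direction cannot be determined. The figures of up to 9 points either way for good outcome and 0.1 to 2.0 points for haemorrhage only show scale under assumed inputs. The conclusion rests on the plain reading of 2.3.2; if the full protocol or flow chart diverts these patients, it reduces to a wording error in the eligibility rule. The document does not support the claim of a systematic imbalance in a known direction, or of a between-group bias that would persist in a properly randomized wake-up comparison with equal access.

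**What to change.** 1. Reconcile 2.3.2 with 2.5.2: state whether patients with large vessel occlusion who go to endovascular treatment are in the comparison. Clinical care need not change.
2. Move the endovascular sentence out of the inclusion list, to the treatment section or to an explicit eligibility rule, whichever reflects the intention.
3. If these patients are in, record baseline large vessel occlusion and any endovascular treatment on the case report form.
4. Stratify or adjust the between-group efficacy and haemorrhage comparisons by baseline occlusion. Do not use endovascular treatment received, because it can depend on the response to rt-PA.
5. Report haemorrhage and within-group change separately for patients with and without baseline occlusion.

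The cost is protocol wording, one or two form fields, slightly more analysis, and less precise rates within each stratum. No extra procedure should be needed, since the plan must already identify occlusion in order to send patients to endovascular treatment. Restricting the main comparison to patients without occlusion is also possible, but it narrows the population and loses patients; stratifying or adjusting keeps everyone.

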#### Exclusion criteria

2.3.3

Patients will be excluded if they meet the following criteria:

Severe patients with malignant hypertension, severe arrhythmia, and acute myocardial infarction;Patients with recent acute infection, trauma, surgery, diabetic ketoacidosis, and hyperosmolar coma;Liver patients with severe primary diseases such as kidney, hematopoietic system, and so on;Patients with tumor and other organ failures.

One of the above is excluded.

### Pretreatment of participants

2.4

#### Collection of clinical data

2.4.1

All hospitalized patients with ischemic stroke have a special clinician responsible for collecting general information on admission. General information collected includes name, age, sex, weight, home address, contact person, contact phone number, previous history of hypertension, diabetes, coronary heart disease, atrial fibrillation, hyperlipidemia, smoking history, drinking history, and so on. Factors, as well as the patient's medication history, epilepsy, migraine, trauma, infection, pregnancy history and imaging data.

#### Grouping method

2.4.2

We will be divided into awakening stroke group (wake group whose morbidity is not exact) and ischemic stroke group (the group clarifying the time of onset) according to whether the onset time of the patient is clear. The awakening group is divided into the awakening group with thrombolytic therapy and the awakening group without thrombolysis according to whether they receive thrombolytic therapy.

#### Laboratory examination

2.4.3

For patients who meet the inclusion criteria, blood routine (white blood cells, hemoglobin, platelets, etc.), biochemistry (liver function, kidney function, myocardial enzymes, blood lipids, and so on), blood coagulation (activated partial thromboplastin time, blood coagulation) time, plasma prothrombin time, and so on), conventional electrocardiogram, chest radiograph and other examinations.

### Intervention method

2.5

#### General treatment

2.5.1

Oxygen inhalation: Patients without hypoxemia do not need routine oxygen inhalation. Monitoring of oxygen saturation <94% or blood gas analysis suggesting oxygen insufflation when hypoxia is indicated. Patients with severe respiratory tract dysfunction are given airway support (tracheal intubation or incision) and ventilator-assisted ventilation.Cardiac function monitoring: Routine electrocardiogram examination should be performed within 24 hours after acute ischemic stroke, and continuous multifunctional electrocardiogram monitor should be given for monitoring if necessary. Drugs that increase the burden on the heart should be avoided.Body temperature management: For patients with elevated body temperature, the cause of fever should be clarified positively. If there is infection, antibiotic treatment is given, and patients with body temperature >38°C should be given cooling treatment.Blood pressure control: Patients with ischemic stroke have elevated blood pressure in the acute phase and generally do not need special treatment. In most patients, blood pressure will drop by itself within 24 hours of onset. If the patient's systolic blood pressure ≥200 mmHg and/or diastolic blood pressure ≥110 mmHg after hospital admission, antihypertensive treatment should be given. Avoid reducing blood pressure too quickly to avoid affecting cerebral perfusion. The blood pressure of thrombolytic patients should be controlled at systolic blood pressure <180 mmHg, diastolic blood pressure <100 mmHg, and blood pressure changes should be monitored dynamically within 24 hours after thrombolysis. If persistent hypotension occurs after stroke, we will actively look for the cause and give treatment such as fluid replacement and boosting.Blood glucose: When blood glucose exceeds 10 mmol/L, insulin hypoglycemic therapy is given. We will adjust the amount of insulin depending on the blood glucose level. We will regularly monitor blood sugar, and control blood sugar to 7.7 ∼ 10mmol/L. When the blood glucose is <3.3 mmol/L, we will give 10% to 20% glucose oral or injection treatment to maintain the blood glucose at a normal level.Nutritional support: Patients who can eat normally do not need additional supplemental nutrition. For those patients with unconsciousness or inability to eat by mouth, we will talk about indwelling gastric tube, nasal feeding liquid food, or enteral nutrition supplements.

#### Treatment solutions

2.5.2

Patients in the defined time-onset group will be given intravenous thrombolysis. The awakening group performs multimodal magnetic resonance imaging (MRI) screening (DWI and FLAIR) on the basis of meeting the pre-set conditions. If the MRI indicates that the DWI-FLAIR does not match, intravenous thrombolytic therapy will be given; if the MRI shows DWI-FLAIR matching, it will be given general treatment. Intravenous thrombolysis uses rt-PA. One-time dosage is 0.9 mg/kg, and the maximum dose does not exceed 90 mg. First, a 10% dose of intravenous bolus was given, and the rest of the dose continued to be infused intravenously for a total of 60 minutes. Thrombolysis is completed in the intensive care unit of the neurology department. During the thrombolysis process, the patient's consciousness and changes in limb muscle strength are closely observed. During this period, we will monitor patients’ vital signs, blood oxygen saturation, and give them treatments such as free radical scavenging and stable plaque. Recheck the computed tomography (CT) of the brain after 24 hours. If no intracranial hemorrhage is found, antiplatelet aggregation treatment (0.1 g oral aspirin tablets) should be given, and acupuncture and rehabilitation should be given after the condition is stable. Patients in the WUS group without thrombolysis received aspirin 300 mg orally as soon as possible after admission, and then changed to 100 mg/day. Other treatment methods will be the same as those of thrombolytic therapy.

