## Discussion

3

Intravenous thrombolytic therapy for ischemic stroke in the ultra-early stage has been proved to be an effective treatment in most randomized trials. However, ultra-early intravenous thrombolysis has a strict treatment time window (onset time <4.5 hours). Exceeding this treatment time window will increase the incidence of symptomatic intracranial hemorrhage, and severe cases may be life-threatening. WUS starts in sleep and is a more common form of ischemic stroke. Its incidence rate can be as high as 25%.^[17]^ Since patients or witnesses cannot provide accurate time of onset, the start time of stroke is still “normal at last.” Therefore, even if the patient or eyewitness finds out, the prescribed time window has already been exceeded. However, some recent research results prove that the original method does not seem appropriate. The study by Kim et al^[18]^ also focused on patients with WUS and stroke patients with unknown onset times during the day without witnesses. He found that nearly half of WUS patients will be immediately awake as soon as clinical symptoms appeared. Roveri et al^[19]^ divided the study subjects into 2 groups, the WUS group and the intravenous thrombolysis group within 3 hours of onset. Early CT manifestations will be applied to the early CT score of the Alberta Stroke Project (ASPECTS), and it was found that regardless of the risk factors and stroke severity Or the ASPECTS score is very close between the 2 groups. There was no statistically significant difference in the early CT scan ASPECTS scores between the 2 groups, indicating that the ischemic event of WUS patients occurred shortly before awakening or awakened as soon as the disease occurred. The author also pointed out that the prognosis of patients in the intravenous thrombolysis group was significantly better than that in the WUS group. The most representative epidemiological evaluation of WUS comes from a 2-center study of 1853 patients with ischemic stroke, including 273 WUS patients. The results show that compared with non-WUS patients, the incidence of WUS patients older age and higher NIHSS score on admission. However, if the time window is not considered, 35% of the patients are suitable for thrombolytic therapy. Then, if we can more accurately assess the onset time of WUS patients, a large number of patients will benefit from thrombolytic therapy. The study found that the mismatch of DWI/FLAIR has a high specificity and sensitivity for the judgment of patients within 3 to 4.5 hours. Thomalla et al^[20]^ observed 543 patients within 4.5 hours of onset. Under the field strength of 1.5 T, the specificity of DWI/FLAIR mismatch judgment of stroke patients within 4.5 hours of onset was as high as 78%. Morelli et al^[21]^ collected 27 WUS patients and 143 non-WUS patients and received intravenous thrombolysis. The results showed that the proportion of patients with mRS ≤1 point was 36.4%. The author mentioned in the conclusion that the selected WUS patients are suitable for intravenous thrombolysis. This study is based on the previous study, and has a purposeful choice for WUS patients who are given thrombolytic therapy. The imaging findings are consistent with DWI/FLAIR mismatch. In summary, we speculate that the selected WUS patients are safer to use intravenous thrombolytic therapy, which is expected to improve the patients’ early efficacy and long-term prognosis. However, whether the statistically significant benefits can be obtained remains to be observed by expanding the sample size. There is no consistent conclusion about the pathogenesis of WUS. WUS is more likely to manifest as small vessel disease. Male patients with sleep apnea are more likely to have WUS, and frequent snoring may be one of the mechanisms of WUS pathogenesis.^[22,23]^ The incidence of WUS patients is relatively high, and the effectiveness and safety of intravenous thrombolysis under the guidance of multimodality imaging treatment of WUS need to be further explored by prospective, large-scale studies.

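### The DWI/FLAIR part of the imaging aim is not supported as written: the eligibility and treatment sections leave no usable mismatch comparison between wake-up and in-window patients, and onset time cannot be verified

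*Protocol article*

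**What the plan says.** The Introduction (section 1) states the imaging aim in two parts. The first concerns dating: "this study will combine the imaging technology to assess the onset time of WUS patients". The second part brings in the known-onset patients as a comparison, since the study is also to "analyze the imaging characteristics of WUS patients and patients within the time window suitable for thrombolytic therapy". The Abstract gives the same aim. The Introduction then closes with a separate efficacy aim: "This study aimed to observe the efficacy of intravenous thrombolysis in WUS patients".

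Four sections bear on whether the imaging aim can be met.

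- **2.3.2 Inclusion criteria** lists "DWI/FLAIR imaging performance mismatch (DWI imaging and FLAIR imaging" as an item, and requires more than 4.5 and less than 12 hours since the patient was last normal. Neither item is limited to one group.
- **2.4.1 Collection of clinical data** includes imaging data among the admission items for all hospitalised ischaemic stroke patients, without naming a modality.
- **2.4.2 Grouping method** divides patients by whether the onset time is clear, then divides the wake-up group by whether thrombolysis is received.
- **2.5.2 Treatment solutions** says "The awakening group performs multimodal magnetic resonance imaging (MRI) screening (DWI and FLAIR) on the basis of meeting the pre-set conditions". Mismatch leads to thrombolysis, and "if the MRI shows DWI-FLAIR matching, it will be given general treatment". For the other group the text is only: "Patients in the defined time-onset group will be given intravenous thrombolysis".

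The Discussion (section 3) defines the treatment window as onset less than 4.5 hours earlier. It reports from a cited imaging study that "the specificity of DWI/FLAIR mismatch judgment of stroke patients within 4.5 hours of onset was as high as 78" per cent.

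**The concern.** A between-group comparison needs the same variable measured in both groups and free to vary in at least one of them. DWI/FLAIR status appears to fail this test. Section 2.5.2 uses it as a measured result that splits the wake-up group, while section 2.3.2 uses it as a condition of entry. It cannot be both for the same patients.

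Two conclusions are at risk. The first is a statement that mismatch is similar in wake-up and in-window patients. That could only come from the entry rule or from scans that the article does not describe. The second is a statement about when wake-up strokes began. That would rest on a surrogate that these patients give no means of checking. The same contradiction also decides whether wake-up patients with a matching MRI can be enrolled at all.

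**Working it through.** No sample size or test result is in dispute, so the check is logical. For each way of reading the sections together, ask who has a DWI/FLAIR result and whether it can vary. I take the known-onset group to be the in-window group of the aim. The article implies this by sending that group to thrombolysis, but does not say so outright.

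| Reading | Wake-up group | Known-onset group | Consequence |
|---|---|---|---|
| A. Section 2.5.2 governs | Match or mismatch, varies | No DWI/FLAIR step described | No comparator result for mismatch |
| B. All of section 2.3.2 applies to everyone | Mismatch only | Empty: in-window means less than 4.5 h, entry needs more than 4.5 h | No in-window group and no matching arm |
| C. Mismatch item applies to everyone, time item to wake-up patients only | Mismatch only (100%) | Mismatch only (100%) | Variable is constant, one margin of the 2×2 table is zero, no matching arm |
| D. Section 2.3.2 applies to wake-up patients only | Mismatch only (100%) | No DWI/FLAIR step described | No comparator result and no matching arm |

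The mismatch comparison fails on every row. Only reading A keeps the matching wake-up patients to whom section 2.5.2 assigns general treatment.

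**Onset time.** Under reading A each screened wake-up patient can be labelled match or mismatch, so the surrogate can be applied. It cannot be checked, because section 2.4.2 defines these patients by an onset time that is not known. Scanning the known-onset group would not close the gap. If all are inside 4.5 hours, they could show how often mismatch is present early (sensitivity), but not how often it is absent late (specificity).

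**Illustration only: why a mismatch label is not a known onset time.** Let p be the share of screened wake-up patients truly within 4.5 hours and s the sensitivity of mismatch. Take the 78% specificity from the Discussion. The documents give neither p nor s; I assume p from 0.35 to 0.60 and s from 0.50 to 0.70. The share of mismatch patients beyond 4.5 hours is

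0.22(1 − p) / [s·p + 0.22(1 − p)].

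- p = 0.35, s = 0.50: 0.143 / (0.175 + 0.143) = 0.143 / 0.318 = 0.45
- p = 0.35, s = 0.70: 0.143 / (0.245 + 0.143) = 0.143 / 0.388 = 0.37
- p = 0.60, s = 0.50: 0.088 / (0.300 + 0.088) = 0.088 / 0.388 = 0.23
- p = 0.60, s = 0.70: 0.088 / (0.420 + 0.088) = 0.088 / 0.508 = 0.17

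The range of 17% to 45% follows from assumed inputs. It does not measure the defect in the comparison.

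**The case against.** The strongest reply is that the aim concerns imaging characteristics, not mismatch status alone. Section 2.4.1 collects imaging data in all ischaemic stroke patients, and section 2.3.2 requires early change to be judged against one third of the middle cerebral artery territory. Lesion site or extent of early change can therefore vary and be compared where recorded. This stands. A reader might infer that the whole imaging aim is unanswerable; the documents do not support that.

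Second, section 2.5.2 does not say that known-onset patients are never scanned. The schedule figure and flow chart are not shown, and an article may leave an imaging schedule to the full protocol. This also stands in part: restriction to one group is what the text describes, not what it states. It does not remove the conflict between sections 2.3.2 and 2.5.2, which is in the text itself.

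Third, no section proposes to estimate the accuracy of mismatch. In context, assessing onset time reads as using mismatch to select wake-up patients. A reader might infer that the trial is a failed accuracy study, or that it treats mismatch as proof of onset within 4.5 hours. Neither is in the text. The Discussion reports a specificity below 100% and only speculates that selected patients are safer to treat. What remains is narrower: the surrogate can be used but not verified here.

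Finally, the 78% is weak support for any calculation. The Discussion describes its source as patients within 4.5 hours of onset, and such a sample alone could not yield a specificity.

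**Conclusion.** The concern holds for the DWI/FLAIR part of the imaging aim. As written, the comparison of mismatch between wake-up and in-window patients has no described comparator, or is fixed by selection, or loses its in-window group. Onset time in wake-up patients can be represented by a surrogate but not verified.

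The size is qualitative: between-group information on mismatch is nil on each of the four readings. This rests on taking the known-onset group as the in-window group, and on there being no undescribed DWI/FLAIR scan in that group. If such scans exist and mismatch is not an entry criterion for that group, a comparison becomes possible, but verification of onset time does not.

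The point deserves correction without being a fatal flaw. The outcomes in section 2.6 are safety, NIHSS and mRS, and none depends on the mismatch comparison. The contradiction over who can enter is nevertheless real and must be reconciled.

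**What to change.** 1. Reconcile the Introduction with sections 2.3.2, 2.4.1 and 2.5.2. State which entry criteria, including the time limits, apply to which group. State that mismatch is a variable measured among screened wake-up patients, not an entry criterion for everyone.
2. Keep a screening log, and report mismatch as a proportion of all screened wake-up patients with a confidence interval.
3. Limit the between-group imaging comparison to features recorded in both groups on the baseline imaging already collected, whatever the modality. One example is extent of early ischaemic change, graded before the one-third-territory and mismatch criteria are applied, so that similarity is not produced by selection. Do not assume a baseline CT in every patient: that is only implied by the instruction to repeat CT at 24 hours.
4. Replace the aim of assessing onset time with selecting by DWI-FLAIR mismatch, and draw no conclusion about onset time or similarity of mismatch.

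The cost is a narrower imaging aim, re-wording of a few sections, a log, and reader time for grading. These steps require no added scan, but the comparison can only be as informative as the baseline imaging common to both groups.
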